### Randomization and masking

2.2

In total, 120 participants will be randomly assigned to 1 of 2 groups in a 1:1 ratio, the MSCs or placebo-controlled groups. Randomization numbers are completed by using the computer-generated list of random numbers. An independent statistician who is involved in neither the treatment nor data collection will randomize assignments in this study. It will be blinded to random allocation of participants to the 2 groups. The final group assignments will be sealed in opaque envelopes. Other than the investigational pharmacist who prepared the study drug, clinical and research staff members will be blinded in this trial. The assessors and statisticians for the data collection and analysis will be also blinded to the assignments.

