#### Secondary outcome

2.4.2

Secondary outcomes will be measured individually at 6 weeks and 3 and 6 months post treatment. Table 2 has provided the time points and specific measurements of data. The mainly secondary outcomes are as follows:(1)Uterine scar thickness and areaThe uterine scar thickness and area will be measured using a transvaginal utrasonography device.(2)Mother's milk and serum will be collected at each visit and the immunoglobulin (IgG, IgA, IgM) and the complement (C3, C4) will be detected by transmission immune turbidity method using automatic biochemical analyzer.

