### Sample size

2.6

The sample size calculation is based on the primary outcome. According to previously published study, the proportion of uterine niche is 78% in women with a history of 1 cesarean delivery.^[17]^ We estimated a power of 90% and a 2-sided 0.05 level of significance, and a drop-out rate of 15% is taken into consideration. Finally, we plan to recruit 120 participants (60 in each group) would detect a 15% relative reduction in the primary outcome.

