### Statistical analysis

2.8

For data analysis, all analyses will be performed according to the intention-to-treat principle. Continuous data will be expressed as mean/standard deviation if it meets normal distribution, otherwise it will be presented by medians/interquartile range; categorical data will be expressed as frequency and percentage. In terms of comparison between the 2 groups, 2-tail Student *t* test for continuous data or the Chi-square test or Fisher exact test for categorical data will be used for outcomes. Relative risks and 95% confidence intervals will be calculated for outcomes. To assess changes of outcome levels over time, an analysis of variance (ANOVA) for repeated measures with post-hoc paired *t* tests or Wilcoxon signed rank test will be used for continuous data. Statistical significance is established at *P* < .05. Statistical analysis will be performed using R 3.0.3.

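### The named repeated-measures ANOVA does not deliver the promised intention-to-treat analysis of the repeated outcomes, given the 15% drop-out the protocol expects

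*Protocol article*

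**What the plan says.** Three sections of the protocol article bear on this.

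- **2.8 Statistical analysis** sets the principle: "all analyses will be performed according to the intention-to-treat principle". It then names the t test, the chi-square or Fisher test and relative risks for comparing the arms. For change over time in continuous data it names "analysis of variance (ANOVA) for repeated measures with post-hoc paired" t tests or Wilcoxon signed rank tests.
- **2.4.2 Secondary outcome** gives the visits: "Secondary outcomes will be measured individually at 6 weeks and 3 and 6 months post treatment". The listed outcomes include scar thickness and area on transvaginal ultrasound, and immunoglobulins and complement in milk and serum.
- **2.6 Sample size** states that "a drop-out rate of 15% is taken into consideration", and that "we plan to recruit 120 participants (60 in each group) would detect a 15% relative reduction in the primary outcome".

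The primary outcome in 2.4.1 is a single yes/no reading, niche present or not at 6 months. The article does not say how a woman without that reading is counted, and it does not say that she is left out.

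**The concern.** An intention-to-treat analysis keeps every randomised woman in her allocated arm. Classical repeated-measures ANOVA works on complete series. A woman who attends at 6 weeks and 3 months but misses 6 months is dropped, and her two valid readings go with her. So for the longitudinal outcomes the principle and the method in the same paragraph pull apart. This is a method the article has chosen, not a detail left for later.

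The loss is more than precision. A woman whose early scans look normal may have less reason to return for another transvaginal scan. If attendance depends on earlier readings, women with complete series are a selected group, and the ANOVA describes them rather than the randomised arms.

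The primary outcome raises a related but weaker question. If women without a 6-month scan are simply left out, a completers' comparison would be reported under an intention-to-treat label.

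**Working it through.** **Inputs from the article.** 60 women per arm; 15% drop-out; control niche rate 78%; 15% relative reduction; 90% power, two-sided 0.05; three visits for the secondary outcomes.

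**1. The plan's own sample size.** The target rate is 0.78 × 0.85 = 0.663, a difference of 0.117. The usual two-proportion formula is n = [1.96 √(2p̄q̄) + 1.2816 √(p₁q₁ + p₂q₂)]² / 0.117², with p̄ = 0.7215. This gives (1.2425 + 0.8055)² / 0.013689 ≈ 306.4, so 307 per arm, or 307/0.85 → 362 after drop-out. The stated 60 does not reproduce. That is a separate and larger problem. It matters here only because 60 cannot be read as a completer requirement of 51 that was then inflated.

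**2. Expected losses.** 0.15 × 60 = 9 per arm (18 in total), leaving 51 per arm.

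**3. Readings discarded by the ANOVA.** It uses 51 × 3 = 153 readings per arm. The article does not give the timing of drop-out, so a range is needed:

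| Assumed timing for all 9 women | Readings attended per arm | Discarded |
|---|---|---|
| Before 6 weeks | 51 × 3 = 153 | 0 |
| Between 6 weeks and 3 months | 153 + 9 = 162 | 9 (5.6%) |
| Between 3 and 6 months | 153 + 18 = 171 | 18 (10.5%) |

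A mixed model uses every attended reading in each row.

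**4. Primary outcome if the missing women are left out.** At the design rates, completers with a niche number 51 × 0.78 = 39.78 (placebo) and 51 × 0.663 = 33.81 (MSCs). The difference is placebo minus MSCs.

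- Completers: 78.0% − 66.3% = +11.7 points (RR 0.85).
- Missing placebo women all without niche, missing MSC women all with niche: 39.78/60 − 42.81/60 = −5.1 points (RR 1.08).
- The reverse: 48.78/60 − 33.81/60 = +24.9 points (RR 0.69).
- All missing counted as niche: 48.78/60 − 42.81/60 = +9.9 points (RR 0.88).

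For scale, the target effect is 0.117 × 60 = 7.0 women per arm, fewer than the 9 expected to be missing.

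**5. Illustrations under assumed attendance.** None of these attendance figures is in the article.

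- *Attendance depends on a 3-month scan.* Assume 3-month and 6-month status agree in 90%, and that 92% of women with a 3-month niche return against 65% of the others. Return probability is then 0.9 × 0.92 + 0.1 × 0.65 = 0.893 with a 6-month niche and 0.1 × 0.92 + 0.9 × 0.65 = 0.677 without. Completers show 82.4% against 72.2%, a difference of 10.2 points (RR 0.88) where the truth is 11.7 (RR 0.85).
- *Drop-outs differ by arm, no true effect.* Assume niche in 50% of placebo drop-outs and 90% of MSC drop-outs. Completers show (0.78 − 0.15 × 0.5)/0.85 = 82.9% against (0.78 − 0.15 × 0.9)/0.85 = 75.9%, a spurious 7.1 points. With 51 per arm the standard error is about 0.080 and the rejection rate about 14%.

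**The case against.** The strongest objection concerns the primary outcome. A chi-square or Fisher test needs only a 6-month status for each woman, and it runs on all 60 per arm once a rule or imputation supplies the missing ones. The article excludes no one, and handling of missing outcomes is commonly left to an analysis plan, which is not shown. This stands. A reader might infer that every named test is confined to completers and that 15% of women therefore leave the primary comparison; the article does not say so. Nor does the allowance for drop-out prove it. Inflating for drop-out protects power without defining the analysis set, and 51 is obtained only by working back from 60.

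Two narrower objections also stand. No earlier scan is lost from the primary comparison, because it uses none. Post-hoc paired tests lose only the affected pair: a woman missing at 6 months still contributes to the comparison of 6 weeks with 3 months, and to any between-arm t test at a visit she attended.

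The illustrations in step 5 can be challenged as well. The article lists scar thickness and area at the early visits, not niche status. The first illustration shifts the estimate by 1.5 points towards no effect, against a standard error of roughly 8.8 points. The second needs drop-out that differs sharply by arm in a trial with blinded staff and assessors. They show what is possible, not what is expected. On power alone, going from 60 to 51 per arm at the stated effect costs about 4 points (roughly 30% to 26%).

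The longitudinal method survives these objections. The article names it, and in its classical form it needs complete series. If the authors use the term loosely for a mixed model, the text should say so.

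**Conclusion.** The point holds for the continuous outcomes followed over time. The named ANOVA conflicts with the intention-to-treat commitment at the drop-out the protocol itself expects: about 9 women per arm excluded, and up to 18 attended readings per arm discarded, depending on when they leave. It is biased if attendance depends on earlier readings; otherwise it only wastes information.

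For the primary outcome the point is conditional. The comparison becomes about 51 against 51 only if no missing-outcome rule exists elsewhere. The documents do not support the stronger conclusion that the primary analysis is already a completers' analysis. Of the primary-outcome figures, only the 9 missing per arm and the bounds of −5.1 to +24.9 points follow from the article's own numbers. The bounds are extremes that take the design rates as holding among completers. The bias and type I error figures depend on assumed attendance.

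The change is worth making because it is specific and nearly free. It does not address the shortfall in sample size.

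**What to change.** **Repeated continuous outcomes (2.8).** Replace the repeated-measures ANOVA and post-hoc paired tests with a linear mixed model with arm, visit and arm-by-visit. Include all randomised women with at least one post-treatment measurement, and report the arm difference with its 95% confidence interval at each visit. The model uses every attended visit and is valid when missingness depends on observed readings.

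**Primary outcome.** State in 2.8 how a woman without a 6-month scan is counted, or point to the document that does. If no rule exists, keep all randomised women by multiple imputation of 6-month niche status, done by arm, from the 6-week and 3-month scar measurements. Give the completers-only test and a tipping-point analysis, including all missing counted as niche, as sensitivity analyses. Do not restrict the set to women who received the injection. Allocation follows consent and the injection comes only after the incision is sutured, so that restriction would drop randomised women.

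**Cost.** Wording and some programming, with no new participants, visits or measurements. The only downside is that the mixed model, and the imputation model if it is needed, must be specified in advance.

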#### Primary outcome

2.4.1

As a primary outcome of this clinical trial, we will evaluate the proportion of participants at 6 months who is found uterine niche in the uterus by transvaginal utrasonography.

The ultrasound examination will be performed using a 4 to 9 MHz convex transvaginal probe of Voluson E8 (General Electric Medical Systems, Chicago, IL). The niche is defined as a triangular anechoic area at the presumed site of incision.^[35]^ The standardized approach for imaging and measuring niche will be used as described in detail in a previous publication.^[12]^ Meanwhile, the following niche parameters, such as width of the triangular hypoechoic scar niche (W), depth of the triangular hypoechoic scar niche (D), length of the triangular hypoechoic scar niche (L), residual myometrial thickness (RMT), on the transection of the uterus will be also measured (Fig. 3). When the niche is not found, only the RMT value will be measured.

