### Adverse events

2.5

On the basis of clinical severity, all adverse events, including mild, moderate, and severe, will be obtained and recorded at baseline and throughout the 6-month follow-up. Every time when follow-up, the participants will come to the interviewing room where the case report form (CRF) with adverse events will be filled with their feedback and the specialist checks. We will focus on the wound infection, endometritis, or other infections occurring up to 6 months after delivery in both groups. To evaluate tumor formation as a delayed reaction, we will test the tumor markers (CA12–5, CA15–3, CA19–9, and carcinoembryonic antigen) at baseline and 6 months. The principal investigator (ZL) will be responsible for managing the adverse events clinically. All adverse events will be reported to the Adverse Events Monitoring Committee.

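### The repeated-measures ANOVA with paired follow-up tests names no treatment-by-visit contrast and, in its classical form, uses only women with every visit; a mixed model would serve the continuous secondary outcomes better

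*Protocol article*

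**What the plan says.** Section 2.8 (Statistical analysis) of the protocol article treats two questions in separate sentences.

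- **Between arms.** "In terms of comparison between the 2 groups, 2-tail Student" t test is named for continuous data, and the Chi-square or Fisher test for categorical data. The next sentence adds: "Relative risks and 95% confidence intervals will be calculated for outcomes".
- **Over time.** "To assess changes of outcome levels over time, an analysis of variance (ANOVA) for repeated measures with post-hoc paired" t tests or the Wilcoxon signed-rank test, for continuous data. No group factor and no group-by-time term is named.

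The section opens with a general rule: "all analyses will be performed according to the intention-to-treat principle".

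The outcomes concerned are in section 2.4.2: "Secondary outcomes will be measured individually at 6 weeks and 3 and 6 months post treatment". They are uterine scar thickness and area, and the immune markers, for which mother's "milk and serum will be collected at each visit and the immunoglobulin (IgG, IgA, IgM) and the complement (C3, C4) will be detected". Section 2.5 adds four tumour markers, the last being "carcinoembryonic antigen) at baseline and 6 months". Section 2.6 allows for 15% drop-out from 60 women per arm.

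**The concern.** Two features of the longitudinal analysis fit poorly with a randomised comparison.

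First, a paired t or signed-rank test asks whether values moved between two visits in the same women. After a caesarean delivery, scar dimensions and immune markers can be expected to move in both arms, and the placebo arm is there to separate that movement from an effect of MSCs. A paired test does not use the placebo arm. If its results are reported arm by arm, a change that is significant under MSCs but not under placebo may be read as a treatment effect, which it is not.

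Second, classical repeated-measures ANOVA needs a complete row for each woman. With three post-treatment visits and drop-out expected, it leaves out women who have usable 6-week or 3-month values. The analysed set then becomes the completers, in a plan that declares intention to treat for everything.

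At stake is the reading of the continuous secondary outcomes and the tumour-marker safety data. The primary outcome is not at stake.

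**Working it through.** The plan gives no figure of its own for the longitudinal analysis, so there is none to reproduce.

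**Inputs from the article:** 60 women per arm and 15% drop-out (section 2.6); three post-treatment time points (section 2.4.2); tumour markers at two time points (section 2.5); the tests named in section 2.8.

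**Step 1: which sentence tests what.**

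| Question | Method named in 2.8 | Compares the arms? |
|---|---|---|
| Niche at 6 months (primary) | Chi-square or Fisher, relative risk | Yes |
| Continuous outcome, between arms | Student t test, no baseline adjustment named | Yes |
| Continuous outcome, change over time | Repeated-measures ANOVA, then paired t or signed-rank | Not as written |

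The primary outcome is one proportion at one time point ("we will evaluate the proportion of participants at 6 months who is found uterine niche in the uterus by transvaginal utrasonography"), so it falls outside the third row. For tumour markers there are only two time points. If the change-over-time sentence is applied to them, a within-arm ANOVA reduces to a paired before/after test. With a group factor, the group-by-time term would equal a between-arm t test on change, but the text does not name one.

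**Step 2: women kept by a complete-case ANOVA.**

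- If the planned drop-out is the whole loss: 60 × (1 − 0.15) = 51 per arm, or 102 of 120. Nine per arm are left out.
- If visits are missed independently with probability q at each of three visits (an assumption; the article gives no such rate), the expected number kept is 60 × (1 − q)³:
  - q = 5%: 60 × 0.857 = 51.4
  - q = 10%: 60 × 0.729 = 43.7
  - q = 15%: 60 × 0.614 = 36.8

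Milk values could be fewer still, since milk exists only during lactation. The article gives no figure for this.

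**Step 3: how a within-arm test behaves when MSCs do nothing.** Assumptions, none from the article: normally distributed change scores with SD 1, the same true mean change in both arms, 51 women per arm, two-sided 0.05, 20,000 simulated trials.

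| Common change (SD) | Paired test significant in MSC arm | Significant in MSC arm only | Between-arm t test on change |
|---|---|---|---|
| 0.2 | 29% | 21% | 5.1% |
| 0.3 | 56% | 25% | 4.9% |
| 0.4 | 80% | 16% | 5.0% |
| 0.5 | 94% | 6% | 5.1% |

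The third column agrees with p(1 − p), where p is the within-arm power: for p = 0.563, 0.563 × 0.437 = 0.246. The between-arm test keeps its 5% level throughout. The paired test responds to the common change and says nothing about treatment.

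**The case against.** The strongest reply is that section 2.8 already has a between-arm test. The Student t test is assigned to the comparison of the two groups, and the ANOVA has a different stated purpose. This stands. A reader might infer that the secondary conclusions rest only on tests that ignore the randomised arms; the between-group sentence rules that out.

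A reader might also infer that the plan deletes every woman with a missed visit and so contradicts its own intention-to-treat rule. The documents do not support that. The article says nothing about deletion, a paired test needs only its own two visits, and a t test at a given visit uses every woman seen then. Handling of missing visits may be set out in a full protocol or analysis plan that is not shown. What remains is a tension, and it arises if the ANOVA is run in its classical form.

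Third, the plan states no rule by which an effect is claimed when one arm is significant and the other is not. The simulated rates therefore show the risk of misreading paired tests. They are not error rates of this plan. Likewise, the 15% is a sample-size allowance and not a minimum loss, and women who leave before 6 weeks have no post-treatment values for any method to use.

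Finally, a repeated-measures ANOVA can carry a group factor. The text neither includes nor excludes one. But the follow-up tests it does name are within-woman, and that is a stated choice rather than a detail left open.

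**Conclusion.** The point holds for the continuous secondary outcomes and the tumour markers, as an improvement that should be made. The method stated for change over time names no treatment-by-visit contrast, and its follow-up tests cannot inform the comparison of MSCs with placebo. The between-arm test that is stated is an unadjusted t test, with no baseline adjustment named even for tumour markers, which are measured at baseline.

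In classical form the ANOVA would use about 51 of 60 women per arm if the planned drop-out is all the loss, and about 44 or 37 under independent missing of 10% or 15% per visit. The first figure assumes that the planned 15% is realised and that nobody else misses a visit. The other two rest on assumed rates. A mixed model would recover only those excluded women who have some post-treatment data, a number that the article does not allow one to estimate.

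**What to change.** In section 2.8, replace the repeated-measures ANOVA for the continuous secondary outcomes with a linear mixed model containing treatment, visit and treatment-by-visit. Use all available visits, with the baseline value as covariate where one is collected. Report the between-arm difference at 6 months with its 95% CI as the treatment comparison.

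Compare the 6-month tumour markers between arms by ANCOVA on the baseline value. Label any paired within-arm tests as descriptive.

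Report milk that is not produced after lactation stops as unavailable, with counts by arm and visit, and do not treat it as ordinary missing data.

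The cost is a change of wording and a few lines of R, with no new data. The mixed model relies on visits being missing at random, which should be stated.

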### Trial status

2.9

The preparation of the study started in December 2016 and the first recruitment started in January 2017. It is anticipated to take 30 months to finish recruiting all the subjects and data collection. Data analysis is expected to be finished a month after data collection. The results will be disseminated via both national and international conferences and formal publication in an academic peer-reviewed journal.

## Discussion

3

During the past decade, many experiments have demonstrated that MSCs have the characteristics of self-renewal and are able to differentiate into adipocytes, osteoblasts, neurons, myoblasts, and endothelium. They have been discovered in muscles, umbilical cord blood, amniotic fluid, and other tissues,^[36]^ and are potent therapeutic sources to repair damaged tissues, such as cardiac tissue, spinal cord injury, and complex perianal fistulas.

Limited clinical trials evidences have supported that MSCs is a safe and effective for refractory disease. A phase I, first-in-man study showed that single intracerebral doses of human neural stem cells were associated with improved neurological function and induced no adverse events.^[37]^ Another phase 3 trials also showed that allogeneic adipose-derived MSCs represented a safe and effective treatment for complex perianal fistulas in patients with refractory Crohn disease.^[38]^ Meanwhile, a pilot trial suggested that autologous MSCs can be safely administered to the hearts with myocardial ischemia and impaired cardiac function.^[39]^ Furthermore, a randomized phase I/II clinical trial demonstrated that intradermal transplantation of autologous stem cells was an effective and safe strategy to promote in vivo mechanical stretch induced skin regeneration, and they can provide complex skin defect reconstruction with plentiful of tissue.^[40]^

Uterine niche, a major public health focus, is a common complication affecting about three-fourths women with previous cesarean section. Most women suffered the postmenstrual spotting and prolonged menstrual bleeding. In this prospective, randomized, double-blind, placebo-controlled with 2 arms study, we hypothesized that MSCs can promote uterine scar reconstruction and reduce uterine niche incidence during cesarean section.

To our knowledge, this trial is the first to investigate the potential of therapeutic use of MSCs for the management of uterine niche after cesarean delivery. The outcomes from this study will help to determine the efficacy and safety of MSCs treatment in uterine niche and bridge the gap with regards to the current preclinical and clinical evidence. Importantly, if a positive outcome is identified, it will provide us with an effective therapeutic strategy to combat uterine niche, and would pave the way for achieving enormous public health benefit.
